(1)	To describe the demographic, social and psychological factors that affect sexual risk behaviors, partner uptake of VCT, family planning intention, infant feeding choices, and HIV serostatus disclosure to sexual partners, among HIV-positive and HIV-negative women attending the Umlazi Section D ANC clinic in Durban, South Africa. 

(2)	To conduct a randomized controlled trial of HIV VCT plus enhanced posttest support as compared to standard HIV VCT among HIV-positive and HIV-negative pregnant women in the Umlazi Section D ANC clinic to determine the independent effect of the intervention on the outcomes listed below, and to determine whether HIV-serostatus to sexual partners influences these intervention effects:
2.1 	Sexual risk of HIV as measured by:  STI incidence (Trichomonas vaginalis, Neisseria gonorrhea and Chlamydia), consistent and correct condom use among HIV-positive and HIV-negative women; and partner uptake of HIV VCT among HIV-positive women.  
2.2. 	Factors that affect mother-to-child transmission of HIV including: acceptance of HIV VCT among HIV-positive and HIV-negative women; acceptance of ARVs, adherence to national infant feeding guidelines, and family planning use among HIV-positive women.
2.3. 	Psychosocial outcomes of PMTCT participation as measured by: perceived social support, emotional distress and partner violence among HIV-positive and HIV-negative women.  
2.4 	With the addition of the legal education and referral component to the intervention study, we will also measure women's awareness of legal rights, awareness of legal recourse, perceived legal needs, uptake of legal assistance and outcome of seeking legal assistance within the 12 month study period. 

(3)	 Additionally, our secondary aim is to compare the following operational outcomes across study arms:  (a) counseling time required; (b) the proportion of women returning for ongoing counseling at 6 and 10 weeks; (c) client's perceived quality of services; (d) the cost of service provision and opportunity costs incurred by clients.
   

Our collaboration includes a multidisciplinary team of researchers from the U.S. and South Africa who will join efforts to test a culturally appropriate and feasible intervention designed to overcome limitations and expand the preventive health benefits of PMTCT programs. Results from this intervention study will be generalizable to other regions of sub-Saharan Africa that are faced with similar challenges related to HIV prevention.

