The second primary aim of the study is to conduct a randomized controlled trial of HIV enhanced post-test support as compared to standard HIV counseling among HIV-positive and HIV-negative women in the Umlazi Section D ANC clinic.  To do this we will randomize 1,495 women at Umlazi Section D ANC in Durban, South Africa to either a comparison or an intervention arm. Women randomized to the comparison arm will receive the standard WHO/CDC HIV pre-and post-test counseling and will have brief follow-up sessions with counselors 6- and 10-weeks postpartum. Women randomized to the intervention arm will receive: 1) a health education video immediately prior to HIV pre-test counseling; 2) pre and post-test counseling sessions that build on the standard protocols by providing more risk reduction counseling, more counseling on disclosure, and PMTCT-related decisions; 3) two additional post-test counseling sessions that coincide with the 6- and 10-week postpartum visits and focus on legal education and referral, partner testing, sexual behavior change and family planning; 4) an active referral to post-test support groups and 6) access to onsite legal support. Women in both arms will be administered a baseline survey at enrolment. Post-intervention assessment will occur at 14 weeks and 9-months post-partum. We will examine the independent effect of the intervention on primary outcomes related to sexual risk transmission of HIV, factors that affect mother-to-child transmission, and psychosocial outcomes of PMTCT participation for women.  We will also examine what influence HIV serostatus disclosure to sexual partners has on these effects.  See Figure 1.    
We have a secondary aim to compare operational outcomes across study arms.   We will compare  counseling time required, proportion of women returning for ongoing counseling at 6 and 10 weeks, clients perceived quality of services and the cost of service provision and opportunity cost incurred by client across the two arms.  This aim will be achieved through analysis of clinic records including counseling log forms and financial records. 

D.2. Study Site and Population

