D.4.7. Post Intervention Assessment: The follow-up assessment will be scheduled to coincide with women's 14 week and 9-month post-partum return visit to the clinic for the Expanded Program on Immunization (EPI).  At 14 weeks, a pap smear will be performed, STI testing will be repeated and a post-intervention behavioral survey will be conducted.  At 9 months post partum, the post-intervention behavioral survey will be repeated. The value of doing the post intervention behavioral assessment twice is that the first time period will capture the immediate intervention effect and the second time period will establish whether or not the behavior change was sustained over time. Both of the surveys will be conducted in a private room at the Umlazi Clinic.  The surveys will also be administered by an interviewer using CAPI (computer assisted personal interview). The survey interviewer will ask the questions and enter the participant's response directly onto a laptop computer. This mode of data capture improves data quality as the data will be entered on the computer one time only.  Each computer will be password protected and locked up at the medical school at the end of each working day.   

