D.5.2.7. Post-test support groups:  Support groups will be facilitated by our staff psychologist. The purpose of these groups is to provide HIV-infected women with a safe place to share their feelings and experiences with other HIV-positive women and a place to access information or resources that they may need. Additionally, the groups will allow all women to talk about issues relating to safe sexual behaviors, pregnancy and post partum care regardless of HIV status.  The staff will facilitate one support group for HIV-positive women and one mixed group for all women (regardless of status).  The groups will meet semi-monthly. New members can join at any time, and attend as many or as few sessions as they wish.  Each session will focus on a specific topic such as disclosure, PMTCT participation, risk reduction, infant feeding and family planning.  However, the role of the facilitator will be to encourage discussion and allow new or re-emerging topics to be discussed by group members.  We will use an active referral system to refer women in the intervention arm to the support groups. VCT counselors will have a schedule of group meeting times and will be able to enroll women directly into one of the two groups.  We will use the current standard practice for these support groups among women in the comparison arm.   

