D.8.2.3. Quality of counseling as perceived by the woman: We will ask 5% of women randomly sampled using exit interviews after their counseling sessions about their perception of the counseling quality that they received.  They will be asked to evaluate the following skills of the counselors viz.  listening, responding with concern and support, supporting decisions and making appropriate referrals using a five-point scale, one being weak and five being strong. In addition, at the 14 week and 9 month assessment, we will ask about their perceived quality of care.   

D.8.2.4. Costs of the standard VCT and the VCT plus post-test support: We will gather information on costs of the intervention from the clinic and the client's perspectives.  We will quantify costs of each element of the counseling and testing process. This will be done through financial records from the clinic.  We will ask clients on the 9-month follow-up survey about costs they may have incurred accessing the services including transportation costs and wages lost during the period of time participants were in the clinic.  

D.8.3. Independent/Predictor/Mediating Measures
D.8.3.1. HIV Serostatus:  We will gather information on women's HIV serostatus from the ANC records.  We have powered the study to be able to stratify all of our analyses by serostatus.  

D.8.3.2. Demographic:  Basic demographic characteristics of participants including age, marital status, educational level, and socioeconomic status will be gathered.  Socioeconomic status will be measured by indicators such as type of roofing and flooring, type of toilet facilities and ownership of radios and televisions.  

D.8.3.3. Parity:  We will ask women about the number of pregnancies that they have had in the past and the number of children who are currently living.  For women who report that they have children we will ask whether any of the children are HIV-infected.  

D.8.3.4. Disclosure to sexual partners: To measure the rates of HIV serostatus disclosure to sexual partners we will ask women who return for the survey interview 9-months post-partum whether they have shared their HIV test results with their primary sexual partner.  

D. 8.3.5. Duration of time since testing:  We will assess the gestational age at which women received testing and the gestational age at delivery to calculate the duration of time between testing and post-intervention assessment.  This information can be gathered from clinic records.  

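### Client costs are collected only at the 9-month survey, some 29 to 51 weeks after the scheduled counselling sessions, although every woman is also due a survey at 14 weeks

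*Protocol*

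**What the plan says.** Specific aim 3 lists, among the operational outcomes to be compared between arms, "the cost of service provision and opportunity costs incurred by clients". Section D.8.2.4 takes the clinic's costs from financial records and the client's costs, including fares and lost earnings, from the women: "We will ask clients on the 9-month follow-up survey about costs they may have incurred". It names no other time for the client items.

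The overview (D1) schedules two surveys: "Post-intervention assessment will occur at 14 weeks and 9-months post-partum". Section D.4.7 says of the 14-week visit that "STI testing will be repeated and a post-intervention behavioral survey will be conducted", and the survey is repeated at 9 months. Section D.8.2.3, immediately before the cost section, uses both occasions: "at the 14 week and 9 month assessment, we will ask about their perceived quality of care".

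After the testing visit, the intervention arm has "two additional post-test counseling sessions that coincide with the 6- and 10-week postpartum visits". The comparison arm has sessions at the same two visits (D.5.2), and D.7 makes them similar in length. The contacts found mainly in the intervention arm are support groups, to which only that arm is actively referred (D.5.2.7: "The groups will meet semi-monthly"), and legal appointments (D.5.2.8). Neither is tied to a particular week.

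Sections D.8.2.1 and D.8.2.2 have counsellors log each counselling session, with start and end times, in both arms.

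**The concern.** Fares, unpaid hours and lost pay are small, routine amounts that are hard to recall many months later. A woman at her 9-month visit is asked about trips made up to a year before, when she has already sat through an interview in the same computer-assisted format at 14 weeks. The document gives no reason for leaving the cost items out of that interview, and it uses the interview for the neighbouring outcome.

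The quality of one named secondary comparison is at stake. As written, the 9-month answers are the only stated source for fares and lost earnings. Whatever is not asked at 14 weeks cannot be recovered at the analysis stage. A woman who completes the 14-week survey and is then lost leaves no client-cost information at all, although the scheduled sessions were already behind her.

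**Working it through.** The protocol states no recall interval, sample size or power for client cost, so there is no figure of its own to reproduce. The check is calendar arithmetic.

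**Inputs**
- First visit: average 28 weeks' gestation (D.2.2), with testing usually offered at that visit (D.2.1).
- Later sessions: 6 and 10 weeks post-partum (D1).
- Surveys: 14 weeks and 9 months post-partum (D1, D.4.7).
- Delivery: 40 weeks, an assumption, with a range of 37 to 42.
- 9 months = 9 × 52.18 / 12 = 39.1 weeks.

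**Formulas**
- Post-partum session: lag = survey week − session week.
- First session: lag = survey week + (delivery week − 28).

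| Session | Lag at 9 months | Lag at 14 weeks |
|---|---|---|
| First visit | 39.1 + 12 = 51.1 weeks | 14 + 12 = 26 weeks |
| 6 weeks | 39.1 − 6 = 33.1 weeks | 14 − 6 = 8 weeks |
| 10 weeks | 39.1 − 10 = 29.1 weeks | 14 − 10 = 4 weeks |

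Delivery at 37 to 42 weeks moves the first-visit lag to 48–53 weeks at 9 months and 23–28 weeks at 14 weeks. Reading 9 months as 36 weeks gives 26, 30 and 48 weeks instead of 29, 33 and 51. The saving from asking at 14 weeks is the same for every session: 39.1 − 14 = 25.1 weeks.

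**Does the recall error have a predictable direction?** Suppose, for illustration, 4 visits common to both arms and 1 extra in the intervention arm, each costing one unit. The true difference is 1. With forgotten fractions f_I (intervention) and f_C (comparison):

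reported difference = 5(1 − f_I) − 4(1 − f_C)

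- f_I = f_C = 0.30: 3.5 − 2.8 = 0.7, too small.
- f_I = 0.20, f_C = 0.30: 4.0 − 2.8 = 1.2, too large.
- f_I = 0.30, f_C = 0.20: 3.5 − 3.2 = 0.3, much too small.
- No extra visit and equal forgetting: 0, whatever the fraction.

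The direction depends on recall fractions that the protocol does not give.

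**Loss between the surveys.** Section D17 expects loss of about 10% per year. If loss is spread evenly in time (an assumption), the 25.1 weeks account for about 10% × 25.1 / 52.18 = 4.8% of women.

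**The case against.** The lags of 29 to 51 weeks belong to visits that both arms make. The post-partum sessions coincide with immunization visits and are of similar length in the two arms, so forgetting them does not by itself create or remove a difference in number of trips. The contacts that can differ, groups and legal appointments, have no fixed week. Some may fall after week 14, where a single 14-week question would miss them. Counselling sessions and their times are logged, and D1 names clinic records, counselling logs and financial records as the sources for this aim. Section D.8.2.4 does not say that women must recall how many visits they made; a cost per trip is an equally possible item. Because D.4.7 repeats the survey at 9 months, the two instruments may share items. Finally, this is one component of a secondary aim, with no hypothesis attached.

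Much of this stands. It rules out the stronger reading that a reader might infer, namely that forgotten visits shrink the arm difference and make the intervention look cheaper to clients than it is. That needs recall fractions and an absence of over-reporting that the document does not supply. Assuming that 10–30% of visits are forgotten equally in both arms, and then concluding that the difference is understated by 10–30%, only restates the assumption.

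The objection does not remove the basic point. The logs are described as holding sessions and times, not fares, wages or waiting time, and nothing says that they will be combined with survey answers. Clinic time also differs between arms at the earliest contact, the one recalled over the longest lag. The additions are about 50 minutes if the 30-minute pre-test extension in D.6 already contains the video (30 + 20), and up to 75 if the video and the 15 extra minutes in D.5.2.2 are counted separately (30 + 15 + 30). Earnings lost through that time are asked about only at 9 months. As for shared items, D.8.2.3 names both surveys and D.8.2.4 names one; if both instruments were meant, D.8.2.4 should say so.

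**Conclusion.** The point holds as a data-collection weakness in a secondary outcome. Client costs are tied to the 9-month survey alone, which puts recall at about 29, 33 and 51 weeks for the scheduled sessions, against 4, 8 and 26 weeks at a survey that already exists. These figures rest on the 28-week average first visit, delivery at 40 weeks and 9 months taken as 39.1 weeks; other reasonable conventions move them by about 3 weeks.

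The resulting error in the client-cost comparison is of unknown size and direction. In addition, women lost between the two surveys, roughly 5% if loss is even over time, give no client-cost data. No primary outcome is affected. This is a cheap improvement, not a flaw that threatens the trial.

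**What to change.** Amend D.8.2.4 so that the same cost items are asked in both arms at both surveys. The 14-week survey would cover services since enrolment, and the 9-month survey services since the 14-week visit. The two are summed for Aim 3(d). Two reference periods also capture group and legal contacts that fall after week 14.

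State that counselling visit counts and session times come from the counselling logs, and legal contacts from the law-clinic records that D.5.2.8 already plans to standardize with the trial's data. The women then need to recall only fares, lost earnings and other time. The protocol describes no attendance record for the support groups, so the survey should ask about them explicitly.

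The cost is a few added questions and a slightly longer 14-week interview. A woman lost after 14 weeks still lacks a full total, but her costs for the scheduled sessions are kept.

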
D.2.2. Study Population:  There are about 9,000 first visit antenatal attendees per year in the ANC clinic at Umlazi Section D Clinic. Women range in age between 16 and 40 years. Approximately 25% are primagravid and the average gestational age at first visit is 28 weeks. Sixty percent of the women at the Umlazi ANC clinic have attended school for at least 8-10 years. Based on the most recent service statistics from the Umlazi Section D clinic, 21,369 women have been offered HIV testing since the program started in June, 2001. Of these women, 18,163 (85%) agreed to be tested, of whom, 8,173 (45%) were HIV infected. The transmission rate from mother to child is 34%, with approximately 95% transmission taking place during the pre and intrapartum period and the remainder post partum, primarily through breastfeeding. The prevalence in the clinic rose from 4% in 1990 to 46% in 2004.  

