D.8.Behavioural and clinical Assessments:  The survey instrument will be developed following standard practices.  The items will be written in Zulu, pre-tested on a few respondents, exit interviews will be conducted to determine if the content was understood as expressed, changes made, and then the survey will be translated into English by an independent translator to determine whether the content remains as planned.  Alterations will then be made, back-translated into Zulu and then pre-testing will be conducted a second time, with approximately 20 representative respondents.  Scales and variables that will be used to measure the key study outcomes such as emotional distress, social support, MTCT acceptance, and partner uptake of VCT will go through another version of refining and re-pilot testing with an additional 20 women. See Appendix 11 for a table of constructs, variables and measures to be used in the survey assessments.  The instrument development will take place during the phase of ethnographic research.  

D.8.1. Primary Outcomes
D.8.1.1. STI Incidence:  Incidence of STIs will be measured and compared among women in the intervention and control arms. Women are screened for a range of STIs upon enrollment to the ANC clinic including (Neisseria gonorrhea, Trichomonas vaginalis, Syphilis, and Chlamydia trachomatis) at baseline.  All women who test positive for any STI are treated immediately.   For the purpose of our study we will measure incidence of Neisseria gonorrhea, Trichomonas vaginalis, and Chlamydia.  These three organisms offer advantages in the evaluation of behavior change interventions in that they are curable with a single-dose treatment regimen and they are sufficiently prevalent in the target population to warrant inclusion.101  All women who return for the follow-up visit 14 weeks post-partum will be re-screened for Neisseria gonorrhea, Trichomonas vaginalis and Chlamydia. All women in the intervention and control arms who are screened for STIs at 14 weeks, will also have a PAP smear done at the time of the cervico-vaginal examination.  Women found to have an STI at this visit will be treated at that visit.   We feel it is important to include a biological outcome as one of our primary study outcomes to measure intervention efficacy. This will enable us to triangulate our findings from self-reported risk behavior data we gather from the women to gain a more complete understanding of behavior change.72  

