D.9.2. Aim 2:  We have conducted power analysis for each primary study outcome.  We have determined that reduction in STI incidence is the factor driving the sample size for the study.  Table 3 below shows the sample size required to detect significant differences in STI incidence across the two arms.  The criterion for significance (alpha) for all power analyses has been set at 0.05.  The tests are 2-tailed, which means that an effect in either direction can be detected and interpreted.   We hypothesize that the intervention will lead to lower rates of STIs. Prevalence data on STIs among pregnant women from KwaZulu-Natal indicate that 52% of women had at least one STI, 12.9% were diagnosed with Chlamydia, 7.8% were diagnosed with Neisseria gonorrhea, and 23% were diagnosed with Trichomonas vaginalis8.  Based on earlier research our team conducted in Durban we established the incident rate of gonorrhea among a periurban sample of ANC attendees in 2000 was 23%.  We have estimated a 22% annual incidence rate of either Neisseria gonorrhea, Trichomonas vaginalis or Chlamydia among HIV-positive women and 18% among HIV-negative women.    Results shown in Table 3 indicate that a sample size of 279 HIV-positive women and 295 HIV-negative women will be adequate to detect a minimum of a 9% difference in rate incident STIs among HIV-positive and an 8% difference among HIV-negative women in the intervention and control arms at the 9-month follow-up assessment.  We feel that this is the minimum level of change that would be meaningful from a policy and program perspective.

Table 3:  Required sample size per arm to detect a difference in STI incidence
STI incidence (base rate)	Effect size (% point change) and Required total sample size per arm	
	.08	.09	.10	
HIV+ women (.22) 	361	279	221	
HIV- women (.18) 	295	226	177	

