The primary purpose of the quantitative data analysis is to conduct a stratified analysis comparing HIV-positive and HIV-negative women randomized to the standard versus the enhanced counseling on the primary study outcomes described in Aim 2.  We have the following primary hypotheses to test intervention effect among women randomized to the intervention as compared to women randomized to the comparison arm at the 9-month post-intervention assessment: (H1) There will be a significant decrease in sexual risk of HIV as measured by STI incidence, correct and consistent condom use and partner testing.  (H2) There will be a significant decrease in mother to child transmission risk as measured by increased uptake of HIV VCT, increased uptake of ARVs, increased adherence to national infant feeding guidelines and increased contraceptive uptake. (3) There will be a significant improvement in psychosocial outcomes associated with PMTCT participation as measured by an increase in perceived social support, and a decrease in emotional distress and partner violence.  Statistics used to test these hypotheses will include comparisons of outcome variables across independent variables using contingency table analysis (log linear Poisson models) with Chi-square tests for significance, t-tests, and F-test for appropriate bivariate differences and multivariable analysis (ordinary least squares multiple regression for continuous outcome variables, and logistic regression for dichotomous outcome variables).  Diagnostic tests for multicollinearity will be conducted prior to multivariable analysis.  All analyses will be conducted separately for HIV-positive and HIV-negative women, given that the baseline rates vary between the two groups and expected change from pre to post-intervention assessment also varies by HIV serostatus.  We will examine how HIV serostatus disclosure to partners influences the effect of the intervention on each study outcome by including HIV serostatus disclosure as a covariate in our analyses. To compare operational outcomes across study arms (Aim 3) we will use contingency table analysis with Chi-square tests for significance and t-tests and F-tests for appropriate bivariate differences.   

D.12. Qualitative data analysis:  

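### The STI sample size uses annual incidence and a 9-month assessment, but STIs are re-tested only at 14 weeks post-partum, so on the plan's own rates power per serostatus stratum is about 47–53%, not the 80% behind Table 3

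*Protocol*

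**What the plan says.** Section D.9.2 says that "reduction in STI incidence is the factor driving the sample size for the study". Its base rates are explicitly annual: "We have estimated a 22% annual incidence rate of either Neisseria gonorrhea, Trichomonas vaginalis or Chlamydia among HIV-positive women and 18% among HIV-negative women". Table 3 enters these as control proportions of 0.22 and 0.18. The selected sizes are 279 HIV-positive and 295 HIV-negative women per arm, for differences of 9 and 8 points. The timing is given as "among HIV-positive and an 8% difference among HIV-negative women in the intervention and control arms at the 9-month follow-up assessment". On error rates, "The criterion for significance (alpha) for all power analyses has been set at 0.05", two-tailed. No power figure appears; D.9.2 and D.9.3 say only that power or sample size is adequate.

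Section D.11 frames the primary hypotheses, including H1 on STI incidence, "as compared to women randomized to the comparison arm at the 9-month post-intervention assessment".

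The schedule differs. Section D.4.7 states: "At 14 weeks, a pap smear will be performed, STI testing will be repeated and a post-intervention behavioral survey will be conducted". At 9 months it lists only a repeat of the behavioural survey. Section D.8.1.1 agrees: "All women who return for the follow-up visit 14 weeks post-partum will be re-screened for Neisseria gonorrhea, Trichomonas vaginalis and Chlamydia". Section D.2.2 gives the starting point of the exposure interval: "the average gestational age at first visit is 28 weeks".

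**The concern.** The sample size and H1 refer to an STI measurement at 9 months that is not scheduled. The swab that is scheduled falls about half a year after enrolment, yet the proportions in Table 3 are one-year figures. A shorter interval means fewer infections in both arms, so the same number of women gives less power.

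STI incidence is the only biological primary outcome and the one that fixes the number enrolled. If its power is misstated, the claims in D.8.3.1 and D.9.3 that the trial can stratify every analysis by serostatus fail for the outcome that set the size.

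**Working it through.** **Inputs.** Annual control rates 0.22 and 0.18; intervention rates 0.13 and 0.10 (differences of 9 and 8 points); 279 and 295 per arm; two-sided alpha 0.05 (all D.9.2 and Table 3). First visit at 28 weeks' gestation (D.2.2). STI re-test at 14 weeks post-partum (D.4.7, D.8.1.1). Assumption: delivery at 40 weeks, range 38 to 42.

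**Step 1: reproduce Table 3.** Pooled normal approximation, no continuity correction, with p̄ = (p1 + p2)/2:

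n per arm = [1.96·√(2p̄(1−p̄)) + 0.8416·√(p1(1−p1) + p2(1−p2))]² / (p1−p2)²

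- HIV-positive, 0.22 vs 0.13: (1.0532 + 0.4491)² / 0.0081 = 278.6, so 279.
- HIV-negative, 0.18 vs 0.10: (0.9618 + 0.4102)² / 0.0064 = 294.1, so 295.

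All six cells match (361/279/221 and 295/226/177). Continuity correction (301 and 319), a one-sided test (220 and 232) and 90% power (373 and 394) do not match. The plan's power is therefore inferred to be 80%.

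**Step 2: exposure to the swab.** (40 − 28) + 14 = 26 weeks. Delivery at 38 to 42 weeks gives 24 to 28 weeks. A swab at 9 months post-partum (39 weeks) would fall at 12 + 39 = 51 weeks and keep about 79% power. The calculation therefore fits a visit at which no swab is taken.

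**Step 3: convert both arms to 26 weeks (t = 0.5 year).** Planned relative reductions: 9/22 = 41% and 8/18 = 44%. Proportional scaling uses p·t. A constant hazard in each arm uses 1 − (1−p)^t.

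Power = Φ{[|p1−p2|·√n − 1.96·√(2p̄(1−p̄))] / √(p1(1−p1) + p2(1−p2))}

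| Stratum (n per arm) | Conversion | Control vs intervention | Power | n per arm for 80% |
|---|---|---|---|---|
| HIV-positive (279) | proportional | 11.0% vs 6.5% | 46.8% | 618 |
| HIV-positive (279) | constant hazard | 11.7% vs 6.7% | 52.6% | 533 |
| HIV-negative (295) | proportional | 9.0% vs 5.0% | 47.8% | 638 |
| HIV-negative (295) | constant hazard | 9.4% vs 5.1% | 52.2% | 569 |

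Over 24 to 28 weeks the same two conversions run from 44% (24 weeks, proportional) to 56% (28 weeks, constant hazard). If 22% and 18% are person-time rates rather than one-year risks, 26-week power is lower still, at 42% and 44%.

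**Step 4: detectable differences at 80% power, with the planned n.** On control incidences of 11.7% and 9.4%, solving the power formula gives 6.6 points (56% relative) and 5.7 points (60% relative). The stated 9 and 8 points would need 9/11.7 = 77% and 8/9.45 = 85% relative reductions.

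**The case against.** **The base rate may be too low.** D.9.2 also quotes 23% gonorrhoea incidence from earlier Durban work, above the 22% and 18% assumed for any of three infections. A reader might infer that the base rate is incoherent. The documents do not show that: the 23% has no time unit and comes from a different sample, a periurban group in 2000. If anything it suggests a higher composite rate, which would raise power. As an illustration with assumed annual rates, 26 weeks, constant hazard in the control arm and the planned relative reductions, 30% gives power of 65% and 76% (HIV-positive, HIV-negative), 35% gives 74% and 83%, and 40% gives 81% and 89%. So a flat claim of 50% power is too strong; the figure is conditional on the plan's own rates. This part of the objection stands.

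**H1 is loosely drafted.** A reader might infer that the STI hypothesis cannot be tested. But the 9-month phrase in D.11 covers all three hypotheses, including HIV-test acceptance and receipt of ARVs, which are recorded earlier. D.4.7 and D.8.1.1 agree on 14 weeks, so the hypothesis is testable then. The time label is wrong, and the power statement attached to it does not carry over.

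**A null result would still say something.** Also true: reductions of 56–60% remain detectable at 80% power, and the outcomes surveyed at 9 months are not affected by the swab date.

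**Can the absolute differences or enrolment rescue the claim?** Holding 9 and 8 points on the shorter-interval base rates would give over 98% power, but only with reductions that the protocol nowhere proposes. Enrolment has no slack: 1,495 × 0.85 tested (D.2.2) × 0.90 retained (reading the D.9.3 attrition figure as retention) is about 1,144, against 2 × (279 + 295) = 1,148.

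**Conclusion.** The concern holds. The detectable differences in D.9.2 and Table 3 belong to roughly a year of exposure, and the scheduled STI test comes at about 26 weeks. On the plan's own rates and relative effects, power is about 47–53% in each serostatus stratum (44–56% over 24 to 28 weeks), and 80% would take about twice the planned n.

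This rests on three assumptions: 80% as the intended power (inferred from the exact match to Table 3), delivery near term, and the planned relative reduction applying over the whole shorter interval. The last is generous, because two of the three enhanced post-test sessions take place at 6 and 10 weeks post-partum, only 8 and 4 weeks before the swab. A higher true incidence would reduce the shortfall.

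A reader might also infer that the primary STI test should pool the two strata. The documents do not support that: D.11 makes the stratified comparison the main purpose and gives a reason, namely that baseline rates and expected change differ by serostatus. A timing mismatch does not overturn that choice.

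**What to change.** - In D.9.2, Table 3 and H1 (D.11), name the 14-week post-partum visit as the STI time point, in line with D.4.7 and D.8.1.1.
- Replace the annual base rates with expected cumulative incidence from enrolment to that visit.
- State the target power, and give the detectable difference or power as a range over the assumed incidence and exposure time. Carry the result into the summary in D.9.3 and the claim in D.8.3.1.
- Give the time basis of the 23% gonorrhoea figure and explain how the 22% and 18% composite rates relate to it.
- Keep the serostatus-stratified analysis. A pooled STI comparison can be no more than an optional supportive analysis.

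This takes protocol wording and a recalculated table, with no new women or specimens. The price is that the stated serostatus-specific STI power becomes less favourable.
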